## Abstract

**Background:**

Insomnia is a highly prevalent disorder causing clinically significant distress and impairment. Furthermore, insomnia is associated with high societal and individual costs. Although cognitive behavioural treatment for insomnia (CBT-I) is the preferred treatment, it is not used often. Offering CBT-I in an online format may increase access. Many studies have shown that online CBT for insomnia is effective. However, these studies have all been performed in general population samples recruited through media. This protocol article presents the design of a study aimed at establishing feasibility, effectiveness and cost-effectiveness of a guided online intervention (i-Sleep) for patients suffering from insomnia that seek help from their general practitioner as compared to care-as-usual.

**Methods/design:**

In a pragmatic randomized controlled trial, adult patients with insomnia disorder recruited through general practices are randomized to a 5-session guided online treatment, which is called “i-Sleep”, or to care-as-usual. Patients in the care-as-usual condition will be offered i-Sleep 6 months after inclusion. An ancillary clinician, known as the psychological well-being practitioner who works in the GP practice (PWP; in Dutch: POH-GGZ), will offer online support after every session. Our aim is to recruit one hundred and sixty patients. Questionnaires, a sleep diary and wrist actigraphy will be administered at baseline, post intervention (at 8 weeks), and at 6 months and 12 months follow-up. Effectiveness will be established using insomnia severity as the main outcome. Cost-effectiveness and cost-utility (using costs per quality adjusted life year (QALY) as outcome) will be conducted from a societal perspective. Secondary measures are: sleep diary, daytime consequences, fatigue, work and social adjustment, anxiety, alcohol use, depression and quality of life.

**Discussion:**

The results of this trial will help establish whether online CBT-I is (cost-) effective and feasible in general practice as compared to care-as-usual. If it is, then quality of care might be increased because implementation of i-Sleep makes it easier to adhere to insomnia guidelines. Strengths and limitations are discussed.

**Trial registration:**

Netherlands Trial register NTR 5202 (registered April 17^st^ 2015).

## Background

Insomnia is a highly prevalent disorder, characterized by difficulty initiating and/or maintaining sleep for at least three nights per week for at least three months, causing clinically significant distress or impairment in daily functioning [1]. One third of the general population shows symptoms of the disorder and about 10 % of the general population meets all criteria of insomnia disorder [2]. The disorder often persists for years [3]. The economic burden of insomnia is considerable; poor sleepers cost around ten times more than good sleepers due to increased healthcare use, work absenteeism and lower work productivity [4, 5]. Insomnia is a significant problem in itself, but it is also associated with the development of other problems. Patients suffering from insomnia are at greater risk of developing comorbid mental health problems such as depression and anxiety [6–9] and of developing cardiovascular problems, contributing to an increased mortality risk [10, 11].

The high prevalence and burden of insomnia calls for (cost-) effective treatment. The most common treatment for insomnia is medication; around 60 % of patients seeing their general practitioner (GP) with complaints of insomnia receive a prescription for benzodiazepines or benzodiazepine-related medication [12, 13]. Meta-analyses have demonstrated that benzodiazepines are effective in enhancing sleep in the short run, but have negative side effects, e.g. headaches, drowsiness, dizziness, dependence [14, 15]. Furthermore, there is limited evidence for the effects of sleep medication used in the long run [16]. There is also little evidence that improvement of sleep persists when sleep medication is withdrawn [17].

Various non-pharmacological alternatives for the treatment of insomnia are available. These treatments can be classified as educational (psycho-education, sleep hygiene), behavioral (relaxation, sleep restriction, stimulus control) or cognitive (paradoxical intention, identifying and challenging dysfunctional thoughts about sleep) [18–23]. Since the 1990s it has become popular to offer those treatments in (various) combinations, referred to as Cognitive Behavioral Therapy for Insomnia (CBT-I). Several reviews have concluded that CBT-I is effective and has longer lasting effects than medication. Even though some side effects might occur in CBT-I, mainly due to more pronounced fatigue because of sleep restriction, those side effects usually pass quickly [24]. Therefore, CBT-I is considered the preferred treatment for insomnia [17, 20, 25–30] and is recommended in several insomnia guidelines (e.g. NICE guidelines [31] and Dutch guidelines [32]). Practice shows that there is a gap between what is advocated by the guidelines (i.e.: CBT-I) and what is offered in practice: despite considerable evidence for the effectiveness of face-to-face CBT-I in general practices [33], GPs tend to prescribe medication. A possible reason is that GPs generally have insufficient time or knowledge to provide the CBT-I themselves [33]. Furthermore, there are not enough qualified psychologists available to offer CBT-I. Online CBT-I may provide a possible solution and enable GPs to offer patients accessible evidence-based treatment. During the past decade, e-health has been introduced steadily into mental healthcare. Many e-health programs have been developed for different disorders [34–36]. Meta-analyses have shown that these (guided) self-help programs, defined largely as standardized therapies that patients work through independently and at their own convenience [37], are effective for a variety of mental health disorders [38]. Meta-analyses on trials on self-help for insomnia [39–42] have shown medium to large effects. A recent meta-analysis showed that effect sizes for online CBT-I were comparable to those of CBT-I delivered face-to-face [43].

In general, e-health treatments are more effective when delivered with some form of guidance or coaching [40, 44, 45]. This guidance can be delivered by non-specialists such as psychology students, nurses or psychological wellbeing practitioners (PWP; in Dutch: POH-GGZ). In the Netherlands almost every GP practice employs a PWP, usually a psychiatric nurse. This offers an excellent opportunity to implement online treatment for insomnia supported by PWPs in the general practice.

The treatment to be investigated in the proposed study, i-Sleep, proved to be feasible, acceptable and effective [42]. However, in this previous study the participants were recruited through a popular website offering information on insomnia to the general public (www.insomnie.nl). This may have resulted in a study population that is, through self-selection, significantly different (e.g., more highly motivated, more technology-savvy) than patients turning to their GP for help. In the proposed study, patients will be recruited via GP referral. This means that we target a population of patients living with insomnia disorder who are actively seeking help, i.e. a representation of general practice. We will examine the (cost-) effectiveness of online guided CBT-I (i-Sleep) from a societal perspective in a direct comparison with care-as-usual.

### Aims and hypotheses

At the moment G.P. care for insomnia is mainly consisting of sleep hygiene and prescribing medication and, therefore, is often suboptimal, i.e. not adhering to guidelines. The objective of this pragmatic trial is to evaluate the effectiveness and cost-effectiveness of an online CBT-I intervention, i-Sleep, for patients with insomnia in comparison with care-as-usual. Patients will receive online coaching by PWPs working in general practices. We expect the intervention to improve the quality of care for insomnia (i.e., lead to higher improvement rates because more people receive care according to the guideline) and to be cost-effective compared to care-as-usual because of low intervention costs, less healthcare utilization and less lost productivity. We expect that patients in the intervention group will show a reduction in insomnia complaints and improved sleep parameters, suffer fewer daytime consequences, and have lower costs related to healthcare utilization and lost productivity than patients in the care-as-usual group.

## Methods/design

### Study design

This study is a pragmatic randomized controlled trial with an economic evaluation from a societal perspective alongside. Patients referring to their GP with insomnia are randomized to either the online intervention group, who will gain access to the guided online intervention, or the control group, who will receive G.P. care-as-usual and will be offered the investigated guided online intervention six months after inclusion. The study protocol, information brochure, questionnaires, recruitment material and informed consent form were approved by the Medical Ethics Committee of the VU University Medical Centre (METC VUmc, registration number 2015/258). The trial is registered with the Netherlands Trial Register (NTR 5202).

### Inclusion and exclusion criteria

Patients aged 18 and over who turn to their GP for help with insomnia complaints are evaluated for eligibility. Inclusion criteria are assessed using a screening questionnaire (t0) and include: difficulty initiating or maintaining sleep for at least 30 minutes a night, for at least three nights a week, for at least three months, causing clinically significant distress and/or impairment in daily functioning, i.e. meeting criteria for a DSM-5 diagnosis of insomnia [1]. Exclusion criteria are: no access to the internet, inadequate proficiency in Dutch, meeting criteria of the diagnosis of sleep apnea (assessed by the GP and in the screening questionnaire using the Screening for Sleeping disorders [46], pregnancy or breast feeding during the trial, working in night shifts, psychological treatment in the last six months, being suicidal (assessed using 5 items from the MINI diagnostic interview [47]), and schizophrenia or psychotic disorder (“Have you been diagnosed with schizophrenia or psychosis?”, to which participants reply ‘Yes’ or ‘No’). Other comorbid psychological disorders and somatic diseases are allowed. The use of (sleep) medication is also allowed and tracked.

### Recruitment

Patients are recruited through general practices. Recruitment leaflets are distributed in waiting rooms, and GPs are instructed to alert insomnia patients to the trial. Patients interested in participating are directed to a website for more information and to leave their contact details. Depending on speed of inclusion, we will also ask GPs to contact patients that presented with insomnia in the 12 months before the start of the trial (database search).

Patients that enrol receive an email containing background information and a link to the screening questionnaire. If eligible, patients are sent an information kit containing a study brochure, sleep diary, actigraphic watch, informed consent form, and stamped return envelope to confirm participation. Patients complete the baseline measurement by filling in a sleep diary and wearing an actigraphic watch for a week. For a detailed representation of participant flow in this trial, see Fig. 1.

**Fig. 1 Fig1:**
[figure not shown]
Schedule of enrolment, interventions, and assessments [75]

Figure 1. Flowchart of the study design.

### Randomization

After inclusion patients are randomized by an independent researcher using random sequence block randomization (blocks of 2, 4 or 6), stratified by whether or not they have used sleep medication in the past 4 weeks and by individual PWP, on a 1:1 ratio. After inclusion of a patient the independent researcher reveals the next randomization outcome. Due to the nature of the study, blinding of the researchers, PWPs or patients is not possible.

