Patients in the intervention condition will receive guidance from a psychological wellbeing practitioner (PWP) in each general practice, usually a (psychiatric) nurse. We will provide training for the PWP in CBT-I as well as in providing online feedback. The training will consists of a 1.5 hour workshop, guided practice with the online course and feedback training. PWPs will be supervised by the first author (TZ) and an experienced CBT psychologist. Patients in both conditions are also allowed to receive care-as-usual from their GP or the PWP.

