### Sample size

In a previous RCT, the i-Sleep intervention demonstrated an effect size of 1.06 on Sleep Quality (Pittsburgh Sleep Quality Inventory, [42]). However, a recent meta-analysis [40] on self-help for insomnia demonstrates somewhat more modest effect sizes; a Hedges’ *g* of 0.80, 0.66 and 0.55 respectively for sleep efficiency, sleep onset latency and wake after sleep onset at immediate post treatment. For the current study we will use a conservative estimation of a post treatment effect size, a Cohen’s *d* of 0.50, on the primary outcome insomnia severity. Using a power of 80 %, an alpha of 0.05, and a study dropout rate of 20 %, we need to include 80 patients in both conditions, 160 in total, to answer our primary research question.

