### Statistical analysis

The study will be conducted in adherence to the Consolidated Standards of Reporting Trials (CONSORT; [65]) statement. For all analyses statistical significance will be set at *p* < .05. In accordance with the intention-to-treat principle, we will use all data independent of treatment or study completion. Missing values will be imputed using multiple imputation for calculation of Cohen’s *d* [66, 67].

Between group interaction effects (time × group) will be tested with Generalized Estimating Equations (GEE). Variables that are not distributed equally or that predict dropout will be added to the model as covariates. This technique is suitable for the analysis of the longitudinal relationship between a continuous outcome variable and several time-dependent and time independent covariates [68].

We will describe the magnitude of the effect (effect size) with Cohen’s *d*. We will calculate this by dividing the difference in scores of the two groups at post-test by the pooled standard deviation of change scores (Cohen’s *d*). This can thus be interpreted as the number of standard deviations the intervention group scores better than the control group [69].

Next, we will compare the intervention and control group with regard to the percentage of patients who have (1) improved and (2) recovered. An ISI score of 10 or lower will be considered recovery. Improvement will be defined as an ISI change score of 7 points or more [50]. This information will be used to calculate the relative risk and the number needed to treat [70].

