There are also potential weaknesses in our study. First of all, it might be a weakness that our intervention lacks any face-to-face contact. We might also have chosen to offer the treatment in blended format where patients receive a combination of online and face-to-face therapy. Blended care might be more acceptable to the patient as well as the professionals and it has been suggested to be effective in other disorders, e.g. depression [74]. However, for this trial we chose not to blend care, because a purely online treatment was deemed more feasible, more cost-effective and easier to implement. A second potential weakness is that we include a convenience sample of GPs. The participating GPs might be more interested in insomnia than those who do not participate. This means that care-as-usual might be of higher quality than provided on average. Also, the participating GPs offer access to a mostly urban population. A third potential weakness is that we include professionals (PWPs) who are currently employed by GPs but who have varying levels of expertise in insomnia and online treatments. Even though we will train the PWPs, and we will supervise them during the trial, it may lead to heterogeneity in the way treatments are delivered. In other words, the high external validity may lead to less internal validity.

Another potential limitation is the fact that we do not establish the DSM diagnosis based on clinical interviews. Patients are referred to us by the GP who establishes clinically relevant sleep problems. The sleep diary, actigraphy and ISI provide us with further information about the severity of the insomnia. Using online questionnaires eliminates the risk of interviewer bias and it ensures relatively easy follow-up measurements while minimizing the burden for participants.

Also, it may be a disadvantage that participants do not gain access to the online treatment immediately: the trial involves a series of practical steps and registration that take some time between enrollment and actual participation. This may influence patients’ motivation negatively.

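### The stated covariate rule selects on observed imbalance or dropout, so the two stratification factors (sleep medication and PWP) are not reliably in the primary ISI model

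*Protocol article*

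**What the plan says.** All references are to the protocol article.

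- **Randomization.** Allocation uses "random sequence block randomization (blocks of 2, 4 or 6") and is "stratified by whether or not they have used sleep medication in the past 4 weeks and by individual PWP, on a 1:1 ratio".
- **Statistical analysis.** The test is described as "Between group interaction effects (time × group) will be tested with Generalized Estimating Equations (GEE"). The covariate rule is "Variables that are not distributed equally or that predict dropout will be added to the model as covariates". The reason given for the method is purely longitudinal: "This technique is suitable for the analysis of the longitudinal relationship between a continuous outcome variable and several time-dependent and time independent covariates". Neither stratification factor is named as a model term.
- **The intervention.** "Patients in the intervention condition will receive guidance from a psychological wellbeing practitioner (PWP) in each general practice". Patients in both arms may also receive usual care from the GP or PWP.
- **Strengths and weaknesses.** PWPs differ in expertise, and despite training and supervision "it may lead to heterogeneity in the way treatments are delivered".
- **Sample size.** With d = 0.50, 80% power, alpha 0.05 and 20% dropout, "we need to include 80 patients in both conditions, 160 in total, to answer our primary research question". No PWP-level variation enters this calculation.

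**The concern.** The design and the covariate rule pull in opposite directions. The trial stratifies on medication use and PWP because they are thought to matter, and stratified blocking then tends to equalise them between arms. A rule that picks covariates because they turned out unequal tends to pass over these two factors. If incomplete blocks leave one unbalanced, or if it predicts dropout, it enters after inspection of the data. In both cases adjustment for the stratifiers depends on what is observed and not on how patients were allocated.

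Two things are at stake, and they act in opposite directions:

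- If the strata predict how much ISI changes, an analysis without them reports a standard error that is too large and gives up some power.
- If the i-Sleep effect differs between PWPs, patients coached by the same PWP are not independent, and a standard error that treats them as independent is too small.

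**Working it through.** **1. The plan's own figure.** A two-sample t-test with d = 0.50, two-sided alpha 0.05 (sidedness is not stated, so two-sided is assumed) and 80% power needs 63.8, so 64 per arm. 64 / 0.80 = 80 per arm, 160 in total. This matches the protocol. The normal approximation gives 63 per arm, then 79 after dropout, 158 in total.

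**2. What cancels.** Suppose stratum j shifts ISI by s_j at baseline and by s_j + δ_j at follow-up. A patient's change then contains δ_j only. With complete data, the time-by-group term compares mean changes, so s_j drops out. A simulation agrees (128 completers, 20 PWPs, PWP variance 0.10, medication effect 0.6 SD, baseline and post-test, exchangeable GEE). Adding medication and PWP as main effects left the interaction estimate and its robust standard error unchanged in all 300 runs (mean SE 0.157, empirical SD 0.157). Only δ_j, or missing data related to the strata, can matter.

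**3. Strata that predict change, left out.** Let R² be the share of the variance of ISI change explained by the strata. The documents do not give it, so 0.01–0.20 is assumed, with balance within strata and unit SD of change. Then:

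- true SE / reported SE = √(1 − R²)
- true alpha = 2[1 − Φ(1.96 / √(1 − R²))]
- power without strata = Φ((0.5/√(2/64) − 1.96) / √(1 − R²))
- power with strata = Φ(0.5/√(2(1 − R²)/64) − 1.96)

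| R² | SE ratio | true alpha | power without strata | power with strata |
|---|---|---|---|---|
| 0.01 | 0.995 | 0.049 | 0.809 | 0.811 |
| 0.05 | 0.975 | 0.044 | 0.814 | 0.827 |
| 0.10 | 0.949 | 0.039 | 0.820 | 0.846 |
| 0.20 | 0.894 | 0.028 | 0.834 | 0.885 |

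**4. i-Sleep effect varying by PWP, treated as independent.** Let m be coached completers per PWP and ρ the ICC in the i-Sleep arm. Neither is given, so m = 2–6 (64/2 = 32 down to 64/6 ≈ 11 PWPs) and ρ = 0.01–0.10 are assumed. The variance factor is V = (1 + [1 + (m − 1)ρ]) / 2. True alpha = 2[1 − Φ(1.96/√V)], power = Φ(0.5/√(2V/64) − 1.96), and total N for 80% power is 2 × 64V/0.80, rounded up per arm.

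| m | ρ | √V | true alpha | power | N for 80% |
|---|---|---|---|---|---|
| 2 | 0.01 | 1.002 | 0.051 | 0.805 | 162 |
| 3 | 0.05 | 1.025 | 0.056 | 0.788 | 168 |
| 4 | 0.05 | 1.037 | 0.059 | 0.779 | 172 |
| 6 | 0.05 | 1.061 | 0.065 | 0.760 | 180 |
| 6 | 0.10 | 1.118 | 0.080 | 0.716 | 200 |

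**5. Both together.** The next check was a simulated unadjusted two-sample t-test with 128 completers, 10–30 PWPs, PWP-by-medication strata, blocks of 2, 4 or 6 and 3,000 runs per setting. The simulated outcome can be read as change in ISI. Type I error was:

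- 0.038–0.048 with a shared PWP variance of 0.05
- 0.032–0.043 with a medication share of 0.10 added
- 0.053–0.067 with PWP variance of 0.05 in the i-Sleep arm only
- 0.046–0.053 with all three sources at 0.05

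The Monte Carlo error is about √(0.05 × 0.95/3000) = 0.004. A further simulation of a complete-case change-score test with 10–20 PWPs gave about 0.02–0.09 across its assumed settings.

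**6. Is exclusion certain?** No. With 10–30 PWPs (assumed) and two medication levels there are 20–60 strata, so 160/60 ≈ 3 to 160/20 = 8 patients each, against blocks of up to 6. Incomplete blocks would be common, so chance imbalance could bring a stratifier in.

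**The case against.** The strongest reply is that this is a condensed article whose analysis plan is not shown. Model terms, random effects and the level of clustering are often left to that plan. The rule says that certain variables will be added, not that nothing else may be. A stratifier that predicts dropout or ends up unbalanced does enter. The lessons are standardised and PWPs are trained and supervised, which argues against a high ICC. The assumed d of 0.50 is below every effect the protocol cites (0.55 to 1.06). The two errors can also largely offset each other.

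Most of this stands, and it limits the point. A reader might infer that the strata are always excluded, that ignoring PWP clustering is a stated decision, or that the trial is underpowered. The documents support none of these. Exclusion is usual but not absolute, the absence of a PWP term is partly an article's silence, and 160 reproduces.

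A reader might also apply 1/√(1 − R²) to stratum effects on the level of ISI, with R² = ICC + (δ/2)²(1 − ICC), where δ is here the medication effect in SD. An ICC of 0.02 with δ = 0.2 gives R² = 0.0298 and a standard error 1.5% too large. An ICC of 0.10 with δ = 0.6 gives R² = 0.181 and 10.5%. That formula describes an unadjusted comparison at one time point. It does not carry over to the stated time-by-group test, where constant stratum effects cancel.

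The reply does not rescue the written rule. Observed imbalance is the wrong criterion for factors balanced by design, and that is stated text.

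**Conclusion.** The point holds as a mismatch between the randomisation and the stated covariate rule. Medication use and PWP will normally be left out of the primary model, or admitted only after the data are seen.

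The numerical effect is modest and its sign is not fixed. Omitting strata that predict change gives a true alpha of 0.049 down to 0.028 and costs about 0.2–5 points of power for R² of 0.01–0.20. A PWP-specific i-Sleep effect treated as independent gives a true alpha of 0.051 up to 0.080 and power of 0.805 down to 0.716. The lowest power needs the extreme corner of the range (6 per PWP, ICC 0.10). At the other corner there is practically no loss.

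All these figures rest on an R², an ICC and a number of PWPs that the documents do not give. The sample size is not in error; its 80% power simply assumes no PWP-level variation in the treatment effect.

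**What to change.** - **Primary model.** Name sleep-medication use in the past 4 weeks and PWP (fixed effect or random intercept) as terms in the ISI model, whatever the observed balance. Let them act on follow-up ISI or on change, through stratifier-by-time terms or an analysis of follow-up scores adjusted for baseline. Main effects alone would leave the time-by-group test unchanged with complete data.
- **Covariate rule.** Drop observed imbalance as the criterion for these two factors.
- **Sensitivity analysis.** Let the treatment effect vary by PWP, through a random slope or a PWP-level robust standard error with a small-sample correction.
- **Economic evaluation.** Include the same stratifiers in the seemingly unrelated regressions. Resampling patients only within PWP would hold the PWPs fixed and would not capture variation in effect between them.
- **Sample size text.** Add one sentence saying that the 80% power assumes no PWP-level variation in the treatment effect.

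The cost is wording only: both variables are recorded for randomisation, and the article reports that recruitment is just starting. The price in the analysis is a few more parameters, and the random slope may not be estimable with few patients per PWP.
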